### Aims and objectives of the study

This pilot RCT seeks to demonstrate the effectiveness of a teacher training programme based on the WHO-EMRO Manual of School Mental Health in improving teacher’s mental health literacy as compared to a waitlist control group. The secondary objective is to evaluate the effect of the WHO-EMRO School Mental Health Manual-based intervention in improving self-efficacy among school teachers. The study will also determine if mental health training of teachers may lead to an indirect improvement in a students’ outcome measure (emotional and behavioral difficulties) and the school psychosocial environment.

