### Participants and sample size

All the teachers in the participating schools of grades 1–10 of both genders will be approached. Exclusion criteria included lack of informed consent, teachers who are leaving/not planning to be in the school in 3 months’ time, and teachers who have not been involved in active teaching in last 6 months. Students of 11–16-years old studying in the participating schools whose parents will give informed consent will also be screened.

A sample size of 220 teachers (110 teachers each in the intervention and control groups) is estimated using 90% confidence interval, 5% absolute precision with expected percentage of improvement on mental health literacy in the intervention group as 10% and the control group as 1% [14].

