### Randomization

Participants will be randomly allocated to the intervention group (receiving school mental health intervention during the study) or the waitlist control group (no training) using computer-generated random numbers. Randomization will be done by a statistician not directly linked to the study using the teachers list provided by the schools. The intervention delivery team will not be involved in the randomization procedure.

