### Statistical analysis

Data will be analyzed using SPSS 20. A description of baseline characteristics of schools and of individuals who participate in the two intervention arms will be compiled using descriptive statistics such as mean and standard deviation, frequency and percentages. Aggregates of the mean item score will be created for each scale at three timelines (baseline T0, immediately following intervention T1, and 3 months following intervention T2). Paired samples’ *t* tests will be used to examine differences in knowledge and attitudes scores and self-efficacy between participants at T0, T1 and T2. Differences in mean scores between the study and control groups will be evaluated using an independent samples’ *t* test. Intention-to-treat analysis will be used for data analysis. Student outcome measures for schools and the psychosocial environment will be compared at baseline and follow-up using the *t* test. Statistical significance will be fixed at a level of *P* < .05. Data on screening, refusals and dropouts will be reported as per Consolidated Standards of Reporting trials (CONSORT) guidelines for participant flow through the trial.

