The aim of this paper is to describe the protocol of a RCT regarding an intervention programme designed to improve teachers’ knowledge, attitude and skills to promote children’s socio-emotional well-being and mental health in the school context in Pakistan. The presented intervention is based on the WHO-EMRO School Mental Health Manual. Specifically, the aim of this pilot RCT is to provide more information on adapting evidence methods for diverse cultures and related school settings. We are not aware of any previous RCT done in Pakistan focusing on teacher training in a whole-school approach. A particular strength of the study is its focus on secondary student’s outcome as well. The limited time available for the study makes the follow-up time of 3 months more feasible rather than 6 months, which might have been more appropriate to observe any significant change. Another limitation of the trial is the generalizability of the results to the Government sector and to elite private schools, which differ significantly in various socio-demographic variables and will not be targeted in this pilot trial. Contamination between teachers in the intervention and control groups may occur when recruiting teachers within the same school and is a limitation of the trial. Findings including the effectiveness and implications from this study will provide information supporting the large-scale RCT for training teachers to increase their mental health literacy and thus potentially improving future school mental health services. In addition, the trial will provide important information about any implementation issues and the extent to which it is likely to be sustainable in different settings in the country. Positive trends result from this trial will hopefully support the urgent work needed in school mental health in Pakistan.

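### Student and school outcomes are tested by an uncontrolled before-after comparison, which cannot answer the stated objective on indirect effects of teacher training

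*Protocol article*

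**What the plan says.** - **Objective** (Aims and objectives of the study): "The study will also determine if mental health training of teachers may lead to an indirect improvement" in students' emotional and behavioural difficulties and in the school psychosocial environment.
- **Unit of randomisation** (Randomization): "Randomization will be done by a statistician not directly linked to the study using the teachers list provided by the schools". Individual teachers are allocated. No stratification by school is stated.
- **Both arms in one school** (Discussion): "Contamination between teachers in the intervention and control groups may occur when recruiting teachers within the same school". This is given as a limitation, and only as contamination between teachers.
- **Students** (Participants and sample size): students 11–16 years "old studying in the participating schools whose parents will give informed consent will also be screened". Neither this section nor Study design gives a student an arm.
- **Timing** (Table 2): the student Strengths and Difficulties Questionnaire (SDQ) and the school profile are collected at baseline and at 3 months.
- **Analysis** (Statistical analysis): for teachers there are paired tests over time and a between-arm test, "Differences in mean scores between the study and control groups will be evaluated using an independent samples" t test. For the other outcomes, "Student outcome measures for schools and the psychosocial environment will be compared at baseline and follow-up using the" t test. That sentence names no comparison group.

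**The concern.** The objective asks about an effect of training, and an effect needs a comparison with what would have happened without it. For teachers the waitlist arm supplies this. For students and schools nothing does, because the randomised groups are teachers who share the same schools.

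A change between baseline and 3 months would then be read as an effect of training when it could be calendar, ageing, retest or regression to the mean. It could also come from the study itself, since some of its activities reach both arms. Procedure for informed consent describes a meeting that presents the manual to the teachers invited to take part, and a letter telling parents about the training. Ethical considerations describes telling teachers and students about a referral route.

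The Discussion presents the student outcome as a strength of the trial. Dissemination says that, if the intervention is found effective, results will go to policy-makers for inclusion in mandatory teacher training. An unsupported student benefit could enter that case.

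**Working it through.** **1. The plan's own figures.** The article gives no sample size, expected change or SD for students or schools. Its only sample size is for teachers, and that reproduces: 1.645² × (0.10 × 0.90 + 0.01 × 0.99) / 0.05² = 108.1, so 109 per arm and 218 in total, against 110 and 220 stated. The point here does not depend on it.

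**2. Is there a randomised contrast for these outcomes?**
- *Schools.* Teachers are allocated individually and the Discussion accepts that both arms occur within a school. No school is designated as a control.
- *Students.* Assume that a student has k teachers, all taking part, each allocated 1:1 independently. The chance of being taught by both arms is 1 − 2 × 0.5^k:

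| k | Taught by both arms |
|---|---|
| 2 | 50% |
| 4 | 87.5% |
| 6 | 96.9% |
| 8 | 99.2% |

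The number of teachers per student is not in the article. Over this range, half or more of the students have mixed exposure.

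**3. What the before-after test does when training has no effect.** Let δ be the natural 3-month drift in units of the SD of the change, and N the number of students. The chance of P < .05 (two-sided) is approximately Φ(δ√N − 1.96). For δ = 0.10 and N = 500 this is Φ(2.236 − 1.96) = Φ(0.276), about 0.61. Exact values from the noncentral t distribution:

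| Drift δ | N = 200 | N = 500 | N = 1000 |
|---|---|---|---|
| 0.05 SD | 0.11 | 0.20 | 0.35 |
| 0.10 SD | 0.29 | 0.61 | 0.89 |
| 0.20 SD | 0.80 | 0.99 | >0.99 |

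Both δ and N are assumptions, and students are treated as independent although they are clustered in classes and schools. The table shows the mechanism. It is not a forecast for this trial.

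**4. School profile.** Study design expects five to six schools and Study setting says seven. A paired t test on 5, 6 or 7 schools has 80% power only for a mean change of 1.68, 1.43 or 1.27 SD of the change. A non-significant result would therefore also say little.

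**The case against.** **The sentence is ambiguous.** It does not say paired. It could mean that groups are compared at baseline and again at follow-up, and the between-arm sentence before it is not expressly limited to teachers. The ambiguity is real, but neither reading helps: a between-group test needs two groups of students or schools, and none is defined.

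**Students can be linked to teachers.** Study design describes the students as taught by the participating teachers, and the teacher questionnaire records which level each teacher teaches. This stands in part, and the full protocol may hold more. But the participating teachers come from both arms, and step 2 shows that most students with several such teachers would be exposed to both.

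**An analysis plan could settle this.** It could refine the student analysis. It could not create control schools.

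**These are secondary outcomes in a pilot, with a hedged aim.** This stands and limits the weight of the point. Still, the article says that the study will determine the matter, and the planned test cannot.

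**Stronger readings that a reader might infer, and that the documents do not support:**
- *That students do not differ at all in exposure.* The share of trained teachers can vary between classes. With k independently allocated teachers per class its SD would be 0.5/√k, that is 0.25 for k = 4 and 0.18 for k = 8. Teachers shared between classes, and adjustment for school, would leave less usable variation.
- *That half of every school's staff is trained.* No stratification by school is stated and only willing teachers enter, so the share may differ between schools and may be below half.
- *That the design contradicts a whole-school claim.* The remark "We are not aware of any previous RCT done in Pakistan focusing on teacher training in a whole-school approach" is a comment on novelty, not a hypothesis under test.
- *That recruiting teachers of grades 1–10 while measuring only 11–16-year-olds is an error.* At most it dilutes an effect.

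**Conclusion.** The concern holds for the student and school outcomes. As written, the plan tests them by an uncontrolled before-after comparison, and neither a significant nor a non-significant result would answer the objective. This rests on the design as stated (individual randomisation, both arms in the same schools, no arm for students or schools) and needs no assumed figure.

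How often the test would mislead cannot be fixed from the article. Under a 0.10 SD drift and no training effect it is roughly 29% to 89% for 200 to 1000 students; over all the assumed drifts and student numbers the range is 11% to more than 99%.

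It would go too far to conclude that the trial as a whole is uncontrolled. Teacher literacy immediately after the intervention is compared between randomised arms, and this point leaves that comparison intact. It should be fixed, but it does not threaten the main result.

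**What to change.** **Change to make**
1. In Aims and objectives, label the student and school outcomes exploratory and remove the wording that the study will determine an effect on them.
2. In Statistical analysis, replace the t test for these outcomes with a description of change from baseline to 3 months, with confidence intervals and no P values, named as an uncontrolled before-after comparison. State that no training effect will be claimed from it.
3. In the Discussion, extend the limitation about both arms sharing a school to the student and school outcomes.

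**Optional addition.** If class timetables can be linked to the allocation list, add an exploratory student analysis. Regress follow-up SDQ total difficulties on the share of a class's teachers allocated to training, adjusting for baseline SDQ and school. Take the P value from re-drawing the teacher allocation exactly as it was randomised, which also handles teachers shared between classes. The article does not describe this link, so feasibility must be checked first.

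**Cost.** The three main changes are wording only and need no extra participants. The trial is underway, so they should be dated and made before the student and school follow-up data are analysed. The student and school claims become weaker. The optional analysis needs timetables from the schools and is likely to be imprecise.

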## Methods

### Study setting

The study setting is private schools located in urban Lahore, having monthly fee structure of less than 3000 Pakistani rupees and matching in broad characteristics like student:teacher ratio, facilities, etc. Seven schools, from inner city areas of Lahore, are likely to be involved in the study in order to achieve the needed sample size.

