### Study design

The study is a two-arm RCT. We expect to include five to six schools to obtain the required sample size. Schools will be sent a letter inviting them to participate. All the teachers in the consenting schools, who are willing to participate, will be recruited for the study. Participants will be randomly allocated to the intervention group (receiving the school mental health intervention during the study) or the waitlist control group (teachers who will not receive any training during the study period) using computer-generated random numbers. In order to evaluate the effectiveness of training, a pre- and post-study design will be used (see the Standard Protocol Items: Recommendations for Interventional Trials (SPIRIT) Diagram in Fig. 1). Participants’ mental health literacy and self-efficacy will be evaluated using questionnaires pre and post training and at 3 months’ follow-up. Students (11–16 years old) taught by these teachers and the school psychosocial environment will also be screened at baseline and 3 months after the intervention using the self-reported SDQ. The study follows the Consolidated Standards of Reporting Trials (CONSORT) Guidelines for the design and implementation of RCTs [15].

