### Intervention

The intervention group will receive a training workshop based on a local adaptation of the WHO-EMRO School Mental Health Manual. The training was adapted in light of in-depth interviews by teachers and school administrators and discussions with relevant stakeholders to make it suitable for the Pakistani school system. The training will be three 6-h sessions delivered face-to-face over a 2-week period. Teachers can decline to participate or withdraw at any stage. Topics to be covered in training workshop are given in Table 1.

**Table 1 Tab1:** Summary of the modules in the World Health Organization, Eastern Mediterranean Region (WHO-EMRO) School Mental Health Manual

Module	Description
Module 1. Social-Emotional Childhood Development	• Developmental tasks of primary-school-age children (6–12 years) • Developmental tasks of secondary-school-age children (12–18 years) • Moral development • Brain development and implications for schooling
Module 2. Mental Health Promoting Schools (Promotion and Prevention)	• Core values of a mental health promoting school • The role of parents in their children’s education • Behavioral management strategies for schools Discipline and management of disruptive behavior Counseling Circle time • Physical health promoting efforts that impact mental health Nutrition Vision/ hearing/ speech Physical exercise • Media and mental health Screen time Internet addiction Cyberbullying • Suicide prevention
Module 3. Addressing Student Mental Health Problems in Your Classroom (and when to refer for additional help)	• Recognizing warning signs for different disorders: Depression Anxiety Pervasive developmental disorders Attention disorders Psychotic disorders Specific learning disorders Intellectual disability Conduct disorders Substance abuse • When to refer to a specialist for evaluation and treatment

The workshop will be conducted by the principal investigator (PI) along with one to two assistants (psychologists trained by the PI). The PI was trained over a period of 2 days by one of the WHO trainers and a Master Trainer of school mental health. ([name]). Participants will be provided with standardized school mental health manual handouts.

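### The student before-after t test ignores that students come from only five to seven schools, so its standard error is wrong whenever schools or classes change differently over the three months

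*Protocol article*

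**What the plan says.** All passages are in the protocol article.

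- **Statistical analysis:** the student measures and the school psychosocial environment "will be compared at baseline and follow-up using the" t test. Whether the test is paired, and whether its unit is the student or the school, is not said. For the arms, "Differences in mean scores between the study and control groups will be evaluated using an independent samples" t test. "Statistical significance will be fixed at a level of" P < .05.
- **Study design:** "Students (11–16 years old) taught by these teachers and the school psychosocial environment will also be screened at baseline" and again three months after the intervention. "We expect to include five to six schools to obtain the required sample size".
- **Study setting:** "Seven schools, from inner city areas of Lahore, are likely to be involved in the study". The two sections together give a range of five to seven schools.
- **Randomization:** teachers are allocated individually, from lists supplied by the schools.
- **Intervention:** "The intervention group will receive a training workshop based on a local adaptation of the WHO-EMRO School Mental Health Manual". It is delivered face to face; the number and size of training groups are not given.

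No school, class or training-group term, mixed model, cluster-robust error, intraclass correlation or design effect appears anywhere. The Discussion names contamination within schools as a limitation, but that is a different problem from correlated data.

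**The concern.** The article names a specific test for the student outcome, so this is a stated method and not a detail left to a later document. Students in one school share teachers, events and the timing of the two surveys. If these move SDQ scores in one school and not in another, the students' changes are correlated. A student-level t test then counts each student as a separate piece of evidence.

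At stake is the claim that training teachers leads to an indirect improvement in students. This is a stated aim, and the Discussion calls the student outcome a particular strength. With a wrong standard error, a result at P < .05 does not carry the error rate that the article attaches to it, and the Dissemination section plans to take positive findings to policy-makers.

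**Working it through.** **1. The plan's own figure.** The 110 teachers per arm follow from the precision formula for a difference of two proportions, with 90% confidence, 5% precision and rates of 10% and 1%:

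n = z²[p1(1−p1) + p2(1−p2)]/d² = 1.645² × (0.0900 + 0.0099)/0.05² = 108.1, so 109 per arm.

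This matches within rounding. The formula has no design effect, and there is no corresponding calculation for students.

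**2. Which correlation matters.** The sentence describes baseline against follow-up. A constant school level cancels in each student's change, so the relevant quantity is the intraclass correlation (ICC) of *change*, not of level.

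**3. Paired student-level test.** Assumptions: m = 50 or 100 students per school; ICC of change 0.01, 0.02 or 0.05; two-sided 5%. The article gives none of these except the 5%.

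Design effect DE = 1 + (m − 1) × ICC; true type I error = 2[1 − Φ(1.96/√DE)].

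| m | ICC of change | DE | True type I error |
|---|---|---|---|
| 50 | 0.01 | 1.49 | 10.8% |
| 50 | 0.02 | 1.98 | 16.4% |
| 50 | 0.05 | 3.45 | 29.1% |
| 100 | 0.01 | 1.99 | 16.5% |
| 100 | 0.02 | 2.98 | 25.6% |
| 100 | 0.05 | 5.95 | 42.2% |

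The correct standard error is √DE times the naive one: from √1.49 = 1.22 to √5.95 = 2.44 times.

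**4. Simulation under no true change.** Settings: 5, 6 or 7 schools with 50 or 100 students each. School-by-time variance is given as a share of score variance, which is not the same scale as the ICC of change.

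| School-by-time variance | Paired test | Unpaired test |
|---|---|---|
| 0 | 4–6% | below 0.5% |
| 0.5% | 13–19% | 1–4.5% |
| 1% | 19–30% | 4–4.5% (m = 50); 9–10% (m = 100) |
| 2% | 28–43% | 9–10% (m = 50); 19–22% (m = 100) |

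A t test on school mean changes rejected in 4–7% throughout.

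The unpaired test can be conservative because it ignores the positive correlation r between a student's two scores. Its naive variance is 2σ²/N, while the true variance is about 2σ²(1 − r)DE/N. It is conservative when (1 − r)DE < 1 and anti-conservative otherwise.

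**5. Why random intercepts alone do not help.** School, class and student intercepts all cancel in the change. In a check with 6 schools, 4 classes each, 25 students per class and school variance of change about 2%, the paired t test and an intercept-only mixed model both gave a standard error of 0.04215. The paired test rejected 24.7% of the time under the null.

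**6. Teachers.** With individual allocation of 220 teachers in six schools and a school ICC of 0.05 to 0.20, the independent-samples t test rejected in 4.5–5.0%. Shared school therefore does no harm to its error rate. Shared training groups in one arm could. The variance ratio is (DE + 1)/2; assumed groups of 20 to 55 with ICC 0.01 to 0.10 give ratios from (1.19 + 1)/2 = 1.10 to (6.4 + 1)/2 = 3.70, and type I errors from 6% to 31%. That range is wide because neither input is in the article.

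**The case against.** **The test may be meant on school means.** The wording about student measures for schools allows it. The 5% level then holds, and precision is the issue. With six schools of 100 students, the standard error of the mean change is √{[ICC + (1 − ICC)/100]/6}, which is 0.058 or 0.100 SD of change at ICC 0.01 or 0.05. Multiplying by 2.571 + 0.920 = 3.49 (t quantiles on 5 df for 80% power) gives a detectable change of about 0.20 to 0.35 SD. So this reading is workable, and nobody should infer that it could detect almost nothing. But the article does not say that this is what is meant.

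**The error rate is conditional.** This stands. A reader might infer that the intervals are too narrow in every case. They are not: a paired test is near 5% if schools do not differ in change, and an unpaired test can err the other way.

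**The inputs are assumed.** This also stands. Cluster sizes and correlations are not in the article, and class is not named as a sampling unit; nesting by class is inferred from students being taught by the study teachers.

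**Student outcomes are secondary and the trial is a pilot.** True, and this limits the weight of the point. A reader might extend it to the primary outcome, teachers' literacy, but shared school does not inflate that comparison and the effect of training groups cannot be sized.

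**The effective sample size.** A reader might take it to be the number of schools. It is N/DE: 600 students with DE of about 2 to 6 count as roughly 300 to 100.

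**Conclusion.** The point holds for the student before-after comparison. As a student-level test, it has the wrong standard error whenever schools or classes change differently over the three months. If paired, its true type I error is about 11% to 42%, assuming 50 to 100 students per school and an ICC of change of 0.01 to 0.05. Only equal change across schools brings it back to about 5%. If unpaired, the direction is not fixed: it ran from far below 5% to 22% in the settings simulated. The article gives no basis for assuming equal change and does not say which test is meant. This should be changed, but it touches a secondary outcome. The teacher analysis needs at most a sensitivity analysis for training group.

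**What to change.** Replace the student-level t test with one of these:

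- a t test on school mean changes in SDQ total difficulties, with n equal to the number of schools; or
- a linear mixed model with a student random intercept and a school-by-time random effect and, where class is recorded, a class-by-time random effect, using small-sample degrees of freedom.

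The time-varying term is essential; intercepts for school, class and student alone would reproduce the paired test's standard error. State the unit of analysis, and that precision is limited mainly by the number of schools. Avoid large-sample cluster-robust errors, which are unreliable with five to seven schools.

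For teachers, record the training group. If there is more than one, add a training-group random effect in the trained arm as a sensitivity analysis. With a single group this effect cannot be estimated.

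The cost is a change of analysis wording plus school, class and training-group labels on the forms. The labels should be set before data collection goes further, since the teacher questionnaires carry no identifying details. The downside is wider intervals and few degrees of freedom. The change corrects the standard error only; it does not turn a before-after comparison into a comparison of arms.
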